#### Strategies to Increase Participation and Decrease Dropouts

Previous intervention studies have indicated that parents might refuse to participate if their children do not receive the interventions and thus do not reap the potential benefits of the interventions. To address this issue, we will adopt the wait-list CG design to ensure that all participants will have an equal chance to undertake the PA training program. The PA training program will be free to the participants, and a 100 Chinese Yuan (US $15.45) coupon will be rewarded to the parent of each participant, which will help to increase participation. In addition, the potential health benefits of the project, such as helping participants decrease body weight and improve HRPF levels, will be clearly described to the participants and their parents to increase their interest in participating.

To reduce dropout rates, rewards (eg, stickers) will be given to participants who complete each intervention session. Stationery (eg, pens, erasers) will be given as a reward to participants who achieve an attendance rate of 85% or higher. In addition, only participants who complete the entire study will receive the 100 Chinese Yuan reward, which will also help to reduce withdrawals.

Establishing effective communication channels with parents will increase their confidence in the project. The participants’ health status (eg, weight change) and session performance will be reported to their parents by messages upon request. In addition, the participating schools will serve as a communication bridge between the research team and participants/parents. Maintaining strong communication with the schools’ PE teachers and nurses will also help the research team to understand the health needs of the participants/parents, which may help to decrease dropout rates.

### Description of Intervention

#### Overview of the Program

The 12-week PA training program will be delivered at a frequency of 2 60-minute sessions per week, with the exercise intensity increasing progressively from 40% heart rate reserve (HRR) to 70% HRR. Each session will consist of both fun game–based aerobic training and resistance training. In addition, the 12-week PA program will be equally divided into 3 levels with different target exercise intensities, and each level will last for 4 weeks. As shown in Figure 2, the target exercise intensity at levels 1, 2, and 3 will be 40%-50% HRR, 50%-60% HRR, and 60%-70% HRR, respectively. In addition, at the beginning of each level, an intensity adaptation period lasting 2 exercise sessions will be given to the participants to help them adapt to the target exercise intensity.

**Figure 2 figure2:**
[figure not shown]
Program overview. HRR: heart rate reserve.

#### Rationale for Developing the PA Program

The program was designed specifically for children with intellectual disability based on international PA guidelines, exercise guidelines, and evidence from previous PA interventions. The following paragraphs introduce the rationale of the design, including the choice of intervention period, frequency, intensity, time, and content of the proposed program.

##### Intervention Period: 12 Weeks

A duration of 12 weeks has generally been recognized as necessary for an effective PA training intervention [19]; the results of our systematic review of intervention studies for decreasing body weight and improving HRPF levels among children with intellectual disability support this selection. Moreover, attrition rates are lower in short-term interventions than in long-term ones [20]. School activities are usually scheduled on a semester basis, and the most commonly adopted length of time of most school activities is 12 weeks. After reviewing local school calendars, we decided that a short-term period of 12 weeks was the most feasible and practical for implementing the intervention.

##### Frequency: 2 Sessions/Week

Our systematic review revealed that most studies delivered PA training at frequencies of either 2 sessions/week (n=11 [21-31]) or 3 sessions/week (n=9 [25,32-39]). Elmahgoub et al [25] explicitly compared the 2 frequencies and reported that both significantly improved health outcomes. No significant differences in the effects were found between the 2 intervention arms, except for in lower limb muscular strength, which was better in the 3 sessions/week arm. However, the participants’ motivation tended to decline at the end of the program in the arm with 3 sessions/week [25]. As a result, a frequency of 2 sessions/week for PA programs for children with intellectual disability will be used.

##### Intensity: 40%-70% HRR, Progressively Increased

Current PA guidelines [40] suggest that MVPA (40%-89% HRR) provides health benefits to children. However, a high intensity and excessive training load can result in an increased risk of sports injuries, and children with insufficient PA and poor HRPF levels might have difficulty adopting high exercise intensities in the early training stages [41]. Therefore, a progressively increasing exercise intensity, from moderate intensity to vigorous intensity, will be used to help children with intellectual disability achieve health benefits in a safer and progressive way.

##### Time: 60 Minutes/Session

The current PA guidelines suggest that 60 minutes of MVPA per session may help children to achieve health benefits [39]. In addition, our systematic review also revealed that PA programs delivered in 60-minute sessions were more likely to be effective.

##### Type: Aerobic Exercise Combined With Resistance Exercise

Evidence from our systematic review suggested that aerobic exercise combined with resistance exercise was the most effective method for reducing obesity [22,25,27,36,42,43] and improving HRPF levels [25,27,36,38,42,43]. Considering that a fun training mode may improve children’s motivation for participation [44], the proposed study will present aerobic exercise in the form of fun games.

#### Program Content

##### Detailed Content of Each Exercise Unit

In the program, each training session (see Figure 3) consists of a warm-up (10 minutes), an exercise unit (45 minutes), and a cooldown (5 minutes). Each exercise unit involves 2 different games (15 minutes each) and 3 resistance training exercises (5 minutes each). Each unit will be delivered for 2 continuous weeks. Hence, 6 exercise units with 12 games and 18 resistance training exercises will be prepared.

**Figure 3 figure3:**
[figure not shown]
Structure of a training session.

Content for the 12 games was selected and modified from the Jockey Club Keep-Fit Formula for Children program [45]. Criteria for selection and modification included being (1) safe for children with intellectual disability, (2) easy to learn, (3) fun, (4) able to achieve the intensity requirements, and (5) feasible to perform in special schools. In addition, we have also prepared 6 alternative and replacement games. The resistance training in this program will focus on muscular strength and endurance of children’s upper limbs, abdominals, and lower limbs. Self-weight exercises (eg, push-ups, sit-ups, and jumping jacks) will be adopted for resistance training because they are safer to perform than exercises that use fitness equipment.

To improve the operability, rationality, effectiveness, suitability, and feasibility of the training program, the training contents will be evaluated by two experts before implementation, considering their vast experience in related areas. The experts will consist of a PE teacher in a local special school with more than 5 years of working experience and an active researcher in the research areas of body weight control and/or physical fitness training for at least 5 years. The two experts will be invited to provide their evaluations in terms of feasibility, effectiveness, and suitability of program content. Effectiveness here refers to the content of games and resistance training exercises that will be able to decrease body weight and improve HRPF levels; suitability refers to the training content that will be suitable for the participants to perform without harmful effects; and feasibility refers to the training program that will be able to be practiced in school settings. Two rounds of evaluation will be conducted. The first round will be implemented to gather detailed opinions about each exercise unit from experts using a 5-point Likert scale (ie, 1=very weak, 2=weak, 3=neutral, 4=good, 5=very good); the experts will also be required to provide comments or suggestions for any item with a score of less than 4. After completing the first-round evaluation, modifications will be conducted according to the experts’ opinions and suggestions. If there are any disagreements or queries/confusion about their opinions, a confirmation letter will be sent to them with appropriate explanations. The second-round evaluation refers to the experts’ final evaluation, in which they will be required to give their final assessment of each exercise unit as a pass or fail (scores ≥4 indicate a pass and scores <4 indicate a fail) [46].

Table 1 summarizes the selected and backup games and resistance training exercises. Multimedia Appendices 2 to 7 present the details of exercise units A to F, and Multimedia Appendix 8 presents the six back-up games.

**Table 1 table1:** Details of the exercise units.

Weeks	Exercise unit	Main games and backup games^a^	Resistance training exercises^b^
1-2	A	1. I’m a Tigger 2. Watch me: dribbling and layup (1)^b^ Backup 1: Cross the tunnel	Handgrips (1); jumping jacks (1); sit-ups (1)
3-4	B	1. Jump, jump, throw 2. Tomb robbing Backup 2: Caterpillar	Push-ups (1); squats (1); burpees (1)
5-6	C	1. Cross the river together 2. Obstacle competition (1)^b^ Backup 3: Flip color disks	Handgrips (2); jumping jacks (2); sit-ups (2)
7-8	D	1. Watch me: dribbling and layup (2)^b^ 2. Rapid team (1)^b^ Backup 4: Reaction by color disk	Push-ups (2); squats (2); burpees (2)
9-10	E	1. Step jumping 2. Rapid team (2)^b^ Backup 5: Run and kick	Handgrips (3); jumping jacks (3); sit-ups (3)
11-12	F	1. Obstacle competition (2)^b^ 2. Funny shuttle run Backup 6: Dodgeball	Push-ups (3); squats (3); burpees (3)

^a^See Multimedia Appendix 8 for a detailed description of backup games.

^b^The number in parentheses indicates the level of the game or exercise.

##### Intensity Monitoring and Control

To ensure that the participants’ exercise intensity level reaches the target requirements, we will calculate their target exercise heart rate (HR) using equations 1 to 3 in Textbox 1 [47]. Resting heart rate (HR_rest_) will be measured using an automated device (Omron M6 [HEM-7000-E]; Omron Corporation) at the beginning of each training level. Maximal heart rate (HR_max_) will be estimated using equation 3 in Textbox 1. In each training session, participants’ real-time exercise HR will be calculated two times by tutors by counting the number of beats on their wrists for 10 seconds and then multiplying by six. If the real-time exercise HR is lower than the lower limit of the target range, appropriate modifications (eg, encouraging them to run faster or jump higher) will be adopted to improve their exercise intensity (see Multimedia Appendices 2 to 7). If the exercise HR is higher than the target range’s upper limit, appropriate modifications (eg, encouraging them to run slower or take a rest) will be implemented as well.

Equations for calculating target exercise heart rate (HR) [47].
**Equations**

Target exercise HR (beats/min) = target % × heart rate reserve (HRR) + resting heart rate (HR_rest_)

HRR (beats/min) = maximal heart rate (HR_max_) – HR_rest_

HR_max_(beats/min) = 210 – 0.56 × age (in years) – 15.5 × (2 [for children with Down syndrome] or 1 [for children without Down syndrome])

The required exercise intensity for each exercise unit must be estimated. Exercise units with predicted lower intensity will be placed at the beginning of the program (eg, level 1). Over time, the required exercise intensity will increase. The intensity of each exercise unit can be controlled by adjusting the running distance, movement speed, or duration of rest intervals. Specific methods for controlling the intensity of each exercise are given in Multimedia Appendices 2 to 7.

##### Safety Assurance

In each training session, the ratio of tutor to participant will be 1:3. Hence, there will be enough tutors to ensure the participants’ safety. The tutors will pay close attention to participants’ exercise performance to prevent sports injuries. In addition, all of the games are from the game series promoted by the Hong Kong Physical Fitness Association. They are recognized as safer than most self-designed games. As different exercise units may have different characteristics, the safety procedures will vary according to the exercises (see Multimedia Appendices 2 to 7). Furthermore, the equipment used in the program will not have sharp edges. It is better to choose equipment that the participants are familiar with or often used in their PE classes. Moreover, drinking times will be arranged in each training session (eg, participants will drink water every 20 minutes). Finally, in case of emergency, at least one PE teacher from each participant school will be required to attend and assist with each exercise session and on-site data collection.

#### Program Delivery

##### Location

The PA training programs will be conducted in the participants’ schools. A fixed sports area in each participating school, such as a basketball court or the indoor activity venue, will be necessary.

##### Training Time Arrangement

The training program session will be scheduled in a non–PE class time slot during school hours. It will be discussed with each participant school.

##### Ratio of PA Instructors to Participants

To ensure that the participants receive individualized instruction but also have interaction opportunities with their peers [48,49], the proposed study will have a high tutor to participant ratio of at least 1:3 for each training session.

##### PA Instructor Recruitment and Training

The tutors should have some knowledge of PE and have experience leading PE courses for students with special needs. Three training sessions (60 minutes per session) will be provided to all tutors. During the sessions, we will explain the background, objectives, and significance of the study and the characteristics of the participants. Then, we will introduce the interventions and the methods for exercise intensity control and safety for each exercise unit. Finally, all of the study measurements will be introduced.

### Description of Control

Initially, no intervention will be delivered to the participants in the CG during the intervention period. Also, they will not be permitted to join any other related programs. They will be asked to continue their usual school activities. All participants in the CG are expected to receive the same PA program after the completion of this study to ensure that they have the same opportunity to improve their health.

### Measures

Obesity- and fitness-related outcomes will be measured as the primary outcomes. Blood pressure will be a secondary outcome. The participants’ demographic information will be collected at baseline and used as a control in data analysis. Moreover, other potential confounders, such as subjective PA level, screen time, sleep duration, eating habits, and pubertal stage, will also be collected and used as controls in data analysis. All of the measurements, except the demographic data, will be collected at baseline (T1), postintervention (T2), and at the 12-week follow-up (T3). A set of evaluation instruments has been drafted.

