#### Primary Outcomes

##### Obesity-Related Outcomes

###### Body Weight

Body weight will be measured with a Tanita body composition analyzer (TBF-410), which is accurate to 0.1 kg. The scale will be cleared before each participant is weighed, and the participants will be asked to look straight ahead and stay still until the digital screen settles before the measurement is recorded. The data reliability can be further increased by using the same scale to measure all of the participants. Body weight will be measured at 3 time points and treated as a continuous variable. Changes in body weight, as an obesity-related outcome, will be calculated and compared between the IG and CG.

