###### BMI

BMI scores will be calculated as weight divided by the square of height (ie, kg/m^2^). Measurement of weight is described in the section above. Height will be measured using a height gauge accurate to 0.1 cm (Harpenden Stadiometer, Holtain Ltd). When measuring heights, the participants will be asked to remove their shoes and stand straight, with knees and feet together. BMI will be evaluated at 3 time points and treated as a continuous variable. Changes in BMI, as an obesity-related outcome, will be calculated and compared between the IG and CG. BMI is also a categorical variable, which will be used for overweight and obese classification.

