###### Waist Circumference

Waist circumference will be measured midway between the lowest rib margin and the top of the iliac crest at the end of a gentle expiration [50] using a flexible meter ribbon accurate to 0.1 cm. Waist circumference will be measured at 3 time points and treated as a continuous variable. Changes in waist circumference, as an obesity-related outcome, will be calculated and compared between the IG and CG. Waist circumference will also be used to estimate the waist-to-height ratio.

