###### Hip Circumference

Hip circumference will be measured at the widest part of the body below the waist [51] using a flexible meter ribbon accurate to 0.1 cm. Hip circumference will be measured at 3 time points and treated as a continuous variable. Changes in hip circumference, as an obesity-related outcome, will be calculated and compared between the IG and CG.

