###### Waist-to-Height Ratio

Waist-to-height ratio will be calculated as waist circumference divided by height. It will be evaluated at 3 time points and treated as a continuous variable. Changes in waist-to-height ratio, as an obesity-related outcome, will be calculated and compared between the IG and CG.

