### Data Analysis

SPSS Statistics (version 23.0; IBM Corp) will be used for the data analysis. Mean (SD) and/or median (IQR) values will be calculated for the continuous variables (eg, BMI). All of the continuous variables at T1 will be tested for between-group differences using an independent sample *t* test. Normality will be checked using Q-Q plots and tested for equal variance, as assessed by Levene’s test. If skewed, the data will be logarithmically transformed before the *t* test is applied. A repeated measures analysis of variance will be used to test for significant differences in the changes in the continuous outcome variables between the 2 groups, where group and time are the 2 factors of interest and will be controlled for significant confounding factors (eg, age). The variables will be selected in a stepwise manner, and only those with *P*<.1 will be kept in the final models. A significance level of .05 will be adopted (2-tailed test). Intention-to-treat analysis will be adopted and performed to avoid bias from withdrawals or protocol deviations.

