If proven effective against obesity and poor HRPF, the intervention design will be made available to the participating special schools so that the intervention can continue to benefit their students. If successful, the program will also be promoted to other local special schools with students with intellectual disability. Furthermore, the study can serve as an example for international researchers, policy makers, and members of the public who are seeking to tackle the problem of obesity and poor HRPF among children with intellectual disability. The aim is to ultimately eliminate the existing health inequities between children with intellectual disability and their TD peers.

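### Eleven unranked outcomes are all primary and each is tested at .05, with a sample size that fits one test and no statement of which result would count as success

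*Protocol article*

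**What the plan says.** The Measures section of the protocol article states: "Obesity- and fitness-related outcomes will be measured as the primary outcomes". Eleven subsections follow under Primary Outcomes.

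- **Obesity-related (6):** body weight, BMI, waist circumference, hip circumference, waist-to-height ratio, body fat percentage.
- **Fitness-related (5):** 6-minute walk distance, 30-second sit-to-stand, 1-minute sit-ups, handgrip strength, sit-and-reach distance.

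Each subsection ends with the same commitment to a between-group comparison of change, for example "Changes in body weight, as an obesity-related outcome, will be calculated and compared between the IG and CG" and "Changes in BMI, as an obesity-related outcome, will be calculated and compared between the IG and CG". No outcome is placed above another.

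Data Analysis plans a repeated measures analysis of variance with group and time as factors for the continuous outcomes, and adds: "A significance level of .05 will be adopted (2-tailed test". The article states no multiplicity adjustment, no testing order and no requirement that several outcomes succeed together. Sample Size Estimation uses one effect size, 0.21, which it does not attach to any outcome. The Discussion makes wider use conditional: "If proven effective against obesity and poor HRPF". No section says what result would meet that condition.

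**The concern.** A .05 level applied to each of 11 primary tests is not the error rate of a conclusion drawn from the set. Because no outcome is ranked and no success criterion is given, emphasis can be chosen after the results are known. This matters here because the Introduction reports inconsistent findings across obesity measures in earlier reviews, and the authors' own meta-analysis could reach no firm conclusion on obesity. A mixed result over 11 equal primaries would leave the same ambiguity, while the article foresees offering the programme to further schools if it is judged effective. The Discussion also calls the sample size sufficient, and that is true only for a single test at .05.

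**Working it through.** **1. The plan's own figure.** Inputs from Sample Size Estimation: effect size 0.21 (taken as Cohen's f), alpha .05, power 80%, correlation 0.5, dropout 20%. From Study Design: 2 groups and m = 3 time points. The article does not name the G*Power procedure. The within-between interaction reproduces its result:

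- Noncentrality λ = f²·N·m/(1−ρ) = 0.0441 × 38 × 3/0.5 = 10.05, with 2 and (38−2)×2 = 72 degrees of freedom.
- Power is 0.800 at N = 38 and 0.776 at N = 36, so 38 completers are needed.
- 38/0.8 = 47.5, rounded up to 48.

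The stated 48 is therefore correct for one group-by-time test at .05.

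**2. Number of primary tests.** 6 + 5 = 11, counting one test per outcome.

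**3. Chance of at least one significant primary result when no outcome has a true effect.** Under independence, two-sided: 1 − 0.95¹¹ = 43.1%. Counting only beneficial results at .025 each: 1 − 0.975¹¹ = 24.3%.

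Independence is only an upper reference. BMI is computed from weight and waist-to-height ratio from waist circumference, so these tests must be correlated. The documents give no correlations, so the values below are assumptions. They were run as multivariate normal draws (at least 300,000 each) on 11 test statistics, with outcomes signed so that benefit is positive.

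| Correlation within obesity / within fitness / between domains | Any significant result | Any beneficial significant result |
|---|---|---|
| 0 / 0 / 0 | 43% | 24% |
| 0.6 / 0.3 / 0.1 | 35.5% | 18% |
| 0.8 / 0.5 / 0.1 | 29.5% | 15% |
| 0.9 / 0.7 / 0.1 | 24% | 12% |
| 0.9 throughout | 13% | 7% |

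Simulating the planned group-by-time F tests at N = 48 gives a similar picture: 43% at zero correlation, 32% at a uniform 0.5, 24% at 0.7 and 20% at 0.8.

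**4. Power if alpha is shared.** Same formula, f = 0.21:

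| Alpha per test | Power at 38 completers | Power if all 48 complete |
|---|---|---|
| .05 (one primary) | 80% | 89% |
| .025 (first Holm step, two primaries) | 71% | 83% |
| .05/11 (Bonferroni over all 11) | 47% | 63% |

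Restoring 80% at 38/0.8-type inflation would take 46 completers (58 enrolled) at .025, or 64 completers (80 enrolled) at .05/11. The last row is not a proposal. It shows that keeping all 11 as primary and correcting afterwards does not fit the planned size.

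**The case against.** Four points against a stronger reading have weight.

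- **Success rule.** A reader might infer that success on any one of the 11 would be declared as proof. The article does not say this. Its conditional sentence, "If proven effective against obesity and poor HRPF", names both domains. If a claim needed at least one significant result in each, the chance under no effect would be (1 − 0.95⁶)(1 − 0.95⁵) = 0.265 × 0.226 = 6.0% with independence, and about 4%, 3% and 2% under the three within-domain settings above. That sentence is discussion prose and not a decision rule, so neither reading can be treated as the plan.
- **Direction.** Wider use would follow only a beneficial result, so the two-sided figures overstate the chance of a false claim of benefit. The right-hand column in the working is the relevant one for that claim.
- **Time points.** A reader might add further inflation for separate tests after the intervention and at follow-up. Data Analysis schedules no such tests; it plans an analysis over all three times.
- **Unseen analysis plan.** Adjustment methods and testing order are often set there, so one can say only that none is stated in the article. The designation of primary outcomes, however, belongs to the protocol, and this article makes it. An unseen plan could add a correction but not the participants it would need: recruitment ran from October to November 2020 with a target of 48.

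**Conclusion.** The concern holds as a fault in what the article fixes: 11 equal primary outcomes, .05 for each, and a sample size for one. Under no true effect, the chance of at least one significant primary result is at most about 43%, about 24% to 35% under the assumed within-domain correlations, and about 13% at a uniform 0.9. For beneficial results only, the range is about 12% to 24%, or 7% at a uniform 0.9. All of these assume one test per outcome, and all but the independence values rest on correlations the documents do not give. No single figure should be quoted as the trial's error rate. The conclusion does not depend on which is chosen, since every one exceeds its nominal level (5% two-sided, 2.5% for benefit). It would be going too far to say that the plan allows roll-out on any one outcome: what counts as proof is simply not defined.

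**What to change.** Before unmasking, by a dated protocol change with the registry entry kept in step:

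1. Name one primary outcome, or one per domain tested by Holm at an overall two-sided .05.
2. State whether the primary test is the group-by-time test or a contrast at a named time point. The power figures above apply to the group-by-time test; a contrast would need its own calculation.
3. Make the remaining outcomes secondary, reported with estimates and confidence intervals.
4. State that effectiveness will be claimed only on the named outcome(s).

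**Cost.** No new measurements are needed, and the article says that statistical analysts are masked, so a change made now would be credible. Results on the other outcomes become supportive only. One named outcome keeps 80% power at 38 completers. Two named outcomes give a worst case of about 71% per outcome at 38 completers, or 83% if all 48 complete, and that should be stated openly because recruitment has closed.
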